#### Participant timeline {13}

See Fig. 2.

**Fig. 2 Fig2:**
[figure not shown]
SPIRIT figure of enrolment, interventions, and assessments. DECT dual-energy-computed tomography, sUA serum uric acid, eGFR estimated glomerular filtration rate, ESR erythrocyte sedimentation rate, CRP C-reactive protein

#### Sample size {14}

This is a differential test, and the primary outcome is the proportion of patients whose renal calculus volume is reduced after 3 months of treatment. A test level with a two-sided *P* value of 0.05 and a power of 80% is assumed, and the ratio of patients’ number in the sodium bicarbonate to the placebo group was 1:1. The parameters of preliminary studies have demonstrated that the reduction rate of renal calculus volume in the test group is 89.74% in 3 months and 64.10% in the control group. The estimated sample size will be 42 in the trial group and 84 in the control group. In this study, the shedding rate does not exceed 15%, and the sample size for each group is determined to be 49.

#### Recruitment {15}

The randomized controlled trial that is blinded to assessors and patients will be conducted at the Shenzhen Traditional Chinese Medicine Hospital and People’s Hospital of Longhua District Shenzhen, wherein medical service would be provided for patients with gout combined with renal calculi. The subjects in this study will be recruited from outpatient and inpatient by placing advertisements on social media platforms of the hospital departments and distributing posters in public areas of the hospital with details of the study and contact information.

Subjects interested will be welcome to contact the investigators by phone or on-site for initial screening. Potential participants would be enrolled, and an appointment was made with a designated physician to examine the inclusion and exclusion criterion. Patients who meet the criteria will be invited to participate in the study, and details of the RCT protocol will be provided. All subjects will be required to sign an informed consent and provide complete information. The subjects will be randomized (1:1) to the placebo and sodium bicarbonate group, and none of the patients would know about their assigned group. Then, the baseline characteristics will be assessed and a database record is obtained by the same physician. All subjects will be treated for 24 weeks and followed up on 4, 12, and 24 weeks, and the data will be evaluated. In addition, all subjects will be given a schedule of intervention dates and follow-up appointments. These evaluations will be performed by an assistant who is involved neither in the randomization nor in the treatment.

#### Assignment of interventions: allocation

##### Sequence generation {16a}

The statistician used the PROC PLAN process of SAS 9.4 statistical software to generate random numbers with block randomization of variable block length.

##### Concealment mechanism {16b}

The mechanism of implementing the allocation sequence; [name] generates the allocation sequence, sequentially numbered, opaque, sealed envelopes, and can be reproduced when needed.

##### Implementation {16c}

[name] (Fujian Medical University School of Public Health) generates the allocation sequence, the doctors will enrol participants, and the nurse will assign participants to interventions.

#### Assignment of interventions: blinding

##### Who will be blinded {17a}

A total of 98 eligible subjects will be randomly assigned to two parallel groups. Statisticians adopt the PROC PLAN process of SAS 9.4 statistical software to generate a random list by randomization of variable block lengths. Then, the clinical trial manager divided them into two groups according to the random list. All people involved including the investigators are blinded to the assignment of the subjects. The placebo is similar to sodium bicarbonate in size, weight, shape, and color. Doctors, subjects, and data analysts are unclear about the type of drug. The randomized assignment sequence is placed in a sealed opaque envelope, and the blind codes are kept in the research management department and can be reproduced when needed.

##### Procedure for unblinding if needed {17b}

Unblinding meetings should be held for whatever reason firstly. Unblinding is realized by connecting offline password letters with e-mail. *Investigator*s will open offline letters to obtain the unblind password, log into the website of unblind system online in non-account login mode directly, and then fill in the relevant information (e.g., subject number, unblinded password) as prompted on the page. After input, the system can associate the electronic letter corresponding to the subject number with the unblinded password and open it to obtain the blind information. The treatment group that subject received will then be displayed on the web page. At the same time, the system will automatically record all the relevant information of the unblinding and inform relevant personnel by message. The code is invalid once used.

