#### Intervention description {11a}

The intervention would be performed for 24 weeks, the 1–12 weeks are double-blinded, and the 13–24 weeks are open-labeled. The volume of renal calculi is slowly decreases and 24 weeks may be needed, while this will lead to the increasing rate of shedding, so the 13–24 weeks are open-labeled.

(1) Sodium bicarbonate group: sodium bicarbonate (1 g tid) will be performed for 24 weeks.

(2) Placebo group: the placebo will be performed for 12 weeks and not be performed from 13 weeks to 24 weeks.

(3) Both groups are administered febuxostat (40 mg/day) for 24 weeks.

(4) Drugs to prevent gout flares: prednisone acetate (5 mg Qd), celecoxib, or colchicine (12 weeks).

(5) During this trial, all subjects will receive general treatment, including ① strict diet: intake of low-calorie diet to maintain ideal body weight. Avoid food with high purine content, such as animal offal, thick gravy soup, sardines, and clams, oysters. The moderate consumption of fish, shrimp, meat, and pea with a moderate amount of purine. The daily diet consists of low purine content of cereal products, fruits, vegetables, milk, dairy products, and eggs. Also, drinking >2000 mL of water every day and give up all kinds of alcohol strictly. ② Avoid inducements including smoking, overeating, cold, dampness, overfatigue, and stress. In addition, it is necessary to slip into comfortable shoes, prevent damage of joint, and only sparingly use drugs that seriously affect uric acid excretion (such as some diuretics). ③ Concomitant disease control: concurrent treatment of concomitant hyperlipidemia, diabetes, hypertension, coronary heart disease, and cerebrovascular disease.

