##### Secondary outcomes

The volume changes of renal calculi, uric acid changes, and the proportion of patients whose sUA levels are <360 μmol/L, the changes in eGFR, the pH value of urine, and adverse effects after 12 and 24 weeks of treatment. Adverse events will be monitored during the 24 weeks of treatment, including the incidence of hypertension before and after treatment, the incidence of post-treatment edema, and the rate of acute gout attack within 12 weeks. Any adverse reactions that occur during the study will be recorded in the “Adverse Reaction Table,” and the patients will be followed up until symptoms disappear or indicators return to normal. In the event of serious adverse events, necessary measures will be taken immediately to ensure the safety of the subjects. In addition to evaluating the primary and secondary outcomes, safety assessment will be conducted at baseline and at 24 weeks after treatment with respect to blood pressure, respiration, heart rate, blood routine, urine routine, liver and renal function, ESR, CRP, and renal DECT.

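### A meeting must precede every code break, with no stated exception for an emergency, so the rule cannot be squared with immediate action where that action depends on the allocation

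*Protocol article*

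**What the plan says.** Four places in the protocol article bear on this.

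- **Procedure for unblinding if needed {17b}.** The opening sentence reads "Unblinding meetings should be held for whatever reason firstly". The technical route follows: the investigator opens a letter to obtain a password and can then "log into the website of unblind system online in non-account login mode directly". The system shows the treatment for that participant, records the event, alerts staff by message and invalidates the code after one use.
- **Who will be blinded {17a}.** "All people involved including the investigators are blinded to the assignment of the subjects". On storage, "the blind codes are kept in the research management department and can be reproduced when needed".
- **Secondary outcomes, under Outcomes {12}.** "In the event of serious adverse events, necessary measures will be taken immediately to ensure the safety of the subjects".
- **Intervention description {11a}.** Of the 24 weeks, "the 1–12 weeks are double-blinded, and the 13–24 weeks are open-labeled".

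**The concern.** An emergency code break exists for the case where a treating doctor needs to know quickly what a participant is taking. Here the opening sentence covers every reason and places the meeting first, so on its plain reading an urgent request waits like any other. The online step that follows looks quick, since it needs no account and concerns one participant. The meeting is therefore the step in {17b} that can add delay.

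What is at stake is mainly participant safety, and whether sites can comply with the protocol as written. A doctor with an urgent need for the code would have to depart either from the unblinding procedure or from the commitment to act at once. The protocol should not leave that choice to be made during the event.

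**Working it through.** No arithmetic applies, because the point depends on no rate, sample size or error level. The check is to set the sections side by side.

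1. **Is the meeting a precondition or merely advice?** The sentence in {17b} applies to any reason and puts the meeting first. The letter and web login come after it. Read in order, the meeting precedes the code.

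2. **Is there an exception elsewhere?**
   - Discontinuing or modifying interventions {11b} lists serious drug-related reactions and investigator-judged adverse events as grounds for leaving, but says nothing on opening the code.
   - Secondary outcomes promises immediate measures without mentioning the code.
   - Who will be blinded {17a} says that the codes can be produced when required, but gives no emergency route and does not lift the meeting rule.
   - The data monitoring committee section {21a} gives that committee no part in unblinding.
   - Adverse event reporting and harms {22} describes symptomatic treatment and drug-specific responses, again with no code break.

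   No section exempts an emergency, sets a time limit for the meeting or says who calls it.

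3. **Does the treating doctor depend on {17b}?** Yes, in weeks 1–12. Investigators are blinded by {17a}, and {17b} is the only described way for them to learn an allocation. In weeks 13–24 treatment is open-label and the placebo group takes no placebo, so the rule matters little.

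4. **When do {17b} and Secondary outcomes collide?** There are two cases in weeks 1–12:
   - *The necessary measure does not depend on the allocation.* It can be taken at once, still blinded. Both sections can be followed.
   - *The necessary measure depends on the allocation.* It cannot be taken until the code is known, and the code cannot be opened until a meeting has been held. The two sections cannot both be followed.

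5. **Is the second case plausible on the document's own terms?** The background {6a} associates alkalized urine with raised blood pressure, salt and water retention and heart failure. Secondary outcomes monitors hypertension and oedema. Section {11b} makes a serious reaction related to the study drug a reason to leave, which calls for a judgment on cause. All participants also receive febuxostat and a flare-prevention drug ({11a}), and {22} attributes different harms to different drugs. An event whose source is unclear without the code is therefore conceivable, although the document describes no specific one.

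6. **Size.** Exposure is limited to participants, among the 98 planned, who have an allocation-dependent emergency in the first 12 of 24 weeks. The document gives no expected number of such events and no duration for the meeting step. Neither can be calculated.

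**The case against.** The strongest reply is that nothing in the text is a direct contradiction. The commitment to immediate measures does not mention the allocation, and the responses in {22} and {11b} are written so that they can be carried out blinded. The document names no event for which a doctor must know whether the participant takes sodium bicarbonate or placebo. This stands in part: the conflict holds only under the condition in step 4, and it would be wrong to say that the two sections clash for every serious adverse event.

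A second reply is that this is a journal article condensed from a fuller approved protocol, which may give the convenor, the timing and an out-of-hours route. That would excuse silence on those details, and their absence is not the point here. It does not excuse a sentence that states the rule and covers all reasons. If the full protocol has an emergency route, this sentence disagrees with it.

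A third reply is that the single-participant access, the log and the single-use code are sound safeguards, and that {17a} points towards access when required. That is right, and the fix relies on those features. They operate only after the meeting, however.

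A reader might also infer three stronger things that the document does not support:

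- **A delay of up to a month.** The only meeting interval stated is the monthly one of the data monitoring committee in {21a}. Section {17b} does not name that committee, and a meeting called for the purpose could be quick.
- **Extra discontinuations and missing week-12 outcomes.** The document does not show this. Section {11b} already lets participants leave for serious drug-related reactions without a code break, so no such loss can be traced to the meeting rule.
- **Harm to all 98 participants.** The rule formally covers all of them, but it affects only those who need an urgent code break.

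**Conclusion.** The point holds in a limited form. The unblinding section makes a meeting the precondition of every code break, and no section shown exempts an emergency. During weeks 1–12, where a serious adverse event calls for a measure that depends on the allocation, that rule and the promise of immediate measures cannot both be kept. The sections should be reconciled.

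The conclusion rests on two things: the plain reading of the opening sentence of {17b}, whose English is awkward but whose scope is clear, and the assumption that an allocation-dependent emergency can occur. The length of the delay and the number of participants affected are unknown. No effect on the primary comparison at 12 weeks is shown. This is a safety-relevant fault in procedure that should be corrected. It is not evidence that the trial's result would be biased.

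**What to change.** Amend Procedure for unblinding if needed {17b} so that it agrees with Secondary outcomes:

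- Require the prior meeting only for non-emergency unblinding.
- For an emergency, allow the investigator to open the code of the one participant concerned through the online system already described, which logs the event, notifies staff and voids the code.
- Hold the meeting afterwards to review and document the reason.
- State that outcome evaluators and data analysts stay masked to that participant's allocation. Because the system notifies staff automatically, say that its message must not disclose the allocation to them.

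This changes the unblinding procedure only and proposes nothing about dose or clinical management. It costs one or two sentences and an approved protocol amendment, and it needs no new system. The downside is that a code becomes slightly easier to break, which the automatic log, single-use access and later review offset.

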#### Data collection and management

##### Plans for assessment and collection of outcomes {18a}

The Case Report Form is used to assess, collect outcome, and baseline. In addition, the clinical trial database is constructed by a designated data manager who is responsible for the regular database management and maintenance. All data will be imported into the clinical trial database by two research assistants.

##### Plans to promote participant retention and complete follow-up {18b}

Follow-up will be conducted at baseline, 4 weeks ± 3 days, 8 weeks ± 3 days, 12 weeks ± 3 days, and 24 weeks ± 3 days. Any missing or incorrect data will be detected by software system. In such case, the original CRFS will be checked to correct or complete every piece of data.

##### Data management {19}

The clinical trial data are managed by [name] (Fujian Medical University School of Public Health) to ensure the authenticity, integrity, and privacy of the data during the research process. The clinical trial database is constructed by a designated data manager who is responsible for the regular database management and maintenance. All data will be imported into the clinical trial database by two research assistants.

##### Confidentiality {27}

The confidentiality measures are as follows. The results of this research project may be published in medical journals. The subject’s information is represented by a unique number, and the coded information is stored in the school of Public Health, Fujian Medical University. The information of subjects will be maintained confidential as required by law. However, records of subjects may be reviewed to ensure that the study complies with applicable laws and regulations.

##### Plans for collection, laboratory evaluation, and storage of biological specimens for genetic or molecular analysis in this trial/future use {33}

Not applicable.

### Statistical methods

#### Statistical methods for primary and secondary outcomes {20a}

The primary outcome will be the comparison between the groups using Pearson’s chi-square test. *t* test, corrected *t* test (equal variance not assumed), and analysis of variance (ANOVA) for repeated measurements will be used for data analysis, and the grade data will be assessed by Wilcoxon two-sample test.

#### Interim analyses {21b}

Doctors will have access to these interim results and make the final decision to terminate the trial.

#### Methods for additional analyses (e.g., subgroup analyses) {20b}

The hybrid control will use multivariate logistic regression, estimating the odds ratio (OR), and 95% confidence interval (CI). Clinically, significant variables in the univariate analysis will be included in the multivariate model. The goodness of fit will be evaluated by Hosmer–Lemeshow test. The statistical analysis was carried out using SPSS (version 26). A two-tailed significance level of 0.05 was used for all tests. *P*<0.05 indicated statistical significance.

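### The supplementary logistic model picks covariates by univariate significance with no limit to baseline variables, and continuous outcomes are analysed without baseline as a covariate or a defined time window

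*Protocol article*

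**What the plan says.** The section on statistical methods for primary and secondary outcomes {20a} fixes the main test: "The primary outcome will be the comparison between the groups using Pearson’s chi-square test". The outcome is read at 12 weeks. For the other data the section lists a t test, an unequal-variance t test, a Wilcoxon test for graded data, and "analysis of variance (ANOVA) for repeated measurements will be used for data analysis". It names no covariate, no set of visits and no contrast.

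The section on additional analyses {20b} adds a multivariable logistic regression giving an odds ratio with a 95% confidence interval. Its rule for filling the model opens with the word Clinically and a comma, and goes on: "significant variables in the univariate analysis will be included in the multivariate model". No variable is named and no restriction to baseline values is stated.

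Two other sections bear on this:

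- Under Outcomes {12}, the changes in stone volume, serum urate and eGFR, and urine pH, are secondary outcomes after 12 and 24 weeks.
- Under Intervention description {11a}, weeks 1–12 are double-blind and weeks 13–24 open-label, and in the control arm "the placebo will be performed for 12 weeks and not be performed from 13 weeks to 24 weeks".

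**The concern.** Randomisation removes the need to search for confounders. Adjustment in a trial serves precision, and for that the covariates should be known to be prognostic and named beforehand. A rule that looks at the outcome first has two weaknesses here.

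- With few patients in the rarer outcome category, the chosen set depends heavily on chance, so the reported odds ratio is conditional on a model nobody could have written down in advance.
- Urine pH and serum urate are measured on treatment, and raising urine pH is how bicarbonate is meant to work. An on-treatment pH value that predicts stone reduction meets the stated rule. Conditioning on it removes the part of the effect that runs through pH.

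For the continuous outcomes, two things are lost. Subtracting baseline, or treating it as one more repeated measurement, uses it less efficiently than conditioning on it. And a group effect averaged over visits up to week 24 would combine a blinded placebo comparison with an open-label comparison against no placebo, which is not the 12-week blinded effect.

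**Working it through.** **1. The plan's own figure.** Sample size {14} gives response rates of 0.8974 and 0.6410, two-sided α of 0.05 and 80% power. With mean rate 0.7692:

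n = [1.960·√(2·0.7692·0.2308) + 0.842·√(0.8974·0.1026 + 0.6410·0.3590)]² / 0.2564² ≈ 41.2, so 42 per arm.

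This reproduces the stated 42. The printed 84 for the control group fits the total under 1:1 allocation. Power is 0.808 at 42 per arm and 0.865 at the planned 49.

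**2. How many covariates the data can carry.** Expected patients without volume reduction:

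- 49 per arm: 49·0.1026 + 49·0.3590 = 5.0 + 17.6 = 22.6
- 42 per arm: 4.3 + 15.1 = 19.4

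Treatment plus two covariates is three coefficients, or 22.6/3 = 7.5 to 19.4/3 = 6.5 patients in the rarer category per coefficient. There is no room for a longer list.

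**3. Screening among baseline-type variables.** Simulation with 49 per arm, the planning rates and 1,000 trials per setting. Assumed, not in the protocol: ten independent candidates, one of them prognostic, screened at p<0.05.

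| Log-odds per SD of the prognostic covariate | 0 | 0.5 | 1.0 |
|---|---|---|---|
| Power, chi-square | 0.88 | 0.86 | 0.86 |
| Power, logistic, covariate fixed in advance | 0.87 | 0.87 | 0.89 |
| Power, logistic, covariates screened | 0.86 | 0.84 | 0.88 |

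At log-odds 0.5 the screen found the prognostic covariate in 41% of trials under the planned effect and 59% under no effect; at 1.0, in 93% and 99%. Type I error was 0.043 to 0.056 across all methods. The Monte Carlo standard error is √(0.05·0.95/1000) ≈ 0.007 for error rates and √(0.86·0.14/1000) ≈ 0.011 for power, so the error rates are compatible with 0.05 and the power differences are small.

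**4. Screening that admits an on-treatment variable.** The planning rates imply a log odds ratio of ln[(0.8974/0.1026)/(0.6410/0.3590)] ≈ 1.59. A second simulation, at 42 per arm, assumed a total log-odds effect of 1.6 and a treatment shift of 1 SD in on-treatment pH. pH passed the screen in 97–100% of trials. Adjusting for it cut the power for treatment from 76% to 24% when half the effect ran through pH, and from 64% to 5% when all of it did. The size depends on these assumptions; the direction does not, provided pH carries some of the effect.

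**5. Baseline as covariate.** With equal variance σ² at both times and correlation ρ, the change score has variance 2σ²(1−ρ), and the baseline-adjusted value has σ²(1−ρ²). The ratio is (1−ρ²)/[2(1−ρ)] = (1+ρ)/2.

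- ρ = 0.5: 0.75, 25% smaller
- ρ = 0.7: 0.85, 15% smaller
- ρ = 0.9: 0.95, 5% smaller

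The protocol gives no ρ.

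**6. Time window.** The primary outcome lies wholly inside the blinded phase. Secondary outcomes are listed at both 12 and 24 weeks, and scheduled visits run to week 24. Section {20a} does not say which visits enter the ANOVA or which term is tested, so an analysis over all visits, crossing the week-12 boundary, is allowed but not stated.

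**The case against.** The strongest reply is that the confirmatory result is untouched. The chi-square is a legitimate test in a 1:1 randomised trial, it matches the sample-size basis, and the screened model sits among additional analyses. With baseline-type covariates, screening did not damage type I error in the simulation, and pre-specified adjustment changed power by only −1 to +3 points at 49 per arm. All of that stands.

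The screening sentence is also garbled and may mean clinically significant variables. Even so, the choice is still made from univariate results. No passage names on-treatment pH or serum urate as a covariate. That is correct: the exposure comes from a rule without a baseline restriction, not from a declared intention.

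Visits and contrasts for the ANOVA are normally settled in an analysis plan, and a group-by-time test would not have the averaging problem. This limits the phase point to a possibility. Volume change already uses baseline by subtraction, but this does not recover the precision of ANCOVA.

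A large adjusted model as the primary analysis would be hard to defend: with about 19 to 23 patients in the rarer category it would be overloaded, and it would turn a comparison of proportions into a conditional odds ratio.

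**Conclusion.** The point holds as a weakness of the supportive and secondary analyses. The stated covariate rule is data-driven, unstable at the expected 19 to 23 patients without reduction, and open to post-baseline variables that would absorb part of the effect. The continuous outcomes forgo a variance reduction of 25% to 5% for an assumed ρ of 0.5 to 0.9 with equal variances, and the ANOVA's time window is open.

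A reader might infer more, but the protocol does not support these readings:

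- *The chi-square and t tests mix blinded and open-label data.* The chi-square is for week 12 only, and nothing says that t tests pool the two time points.
- *The error rate is shown to be wrong.* The simulated 0.043 to 0.056 is compatible with 0.05. That result covers baseline-type covariates only.
- *A centre term is required.* There are two hospitals, but the sequence is described only as "block randomization of variable block length", with no stratification stated.
- *Chi-square statistics will be averaged over imputations.* The protocol says only that multiple imputation is used.

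**What to change.** In section {20b}, delete the univariate screen. Name one or two baseline covariates in advance, for example log baseline stone volume, and exclude any variable measured after randomisation. Keep this logistic model supportive to the unadjusted week-12 chi-square, which remains primary.

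In section {20a}, analyse stone volume, serum urate and eGFR by ANCOVA on the baseline value, using the log scale for volume with a rule fixed beforehand for stones that have disappeared (volume zero). Estimate week 12 (blinded) and week 24 (open-label, supportive) as separate contrasts.

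The cost is a change of wording and slightly more analysis work. Baseline stone volume, serum urate and renal function are already recorded, and the sample size does not change.
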